### **Interventions**

Following randomization women in the intervention groups will see the study acupuncturist based at the IVF centers, or at close proximity to the IVF centers. The acupuncturists are registered with national professional associations, and with a minimum of 2 years clinical experience. Training will be provided to all study acupuncturists on the treatment protocol, practitioner intent or treatment aspirations, recording of treatments administered, the acupuncturists’ duty and an explanation of proposed future monitoring. The treatment protocol was based on two rounds of a Delphi process, with consensus achieved on a treatment protocol for the study. Nineteen acupuncturists participated in this process, with practitioners from Australia (6), China (2), Denmark (1), Sweden (1), the United States (4), and the United Kingdom (1). All women will undergo a traditional Chinese medicine (TCM) diagnosis. The initial diagnosis and treatment will take 60 to 90 minutes undertaken on days 6 to 8 of the stimulated IVF cycle. Two treatments will be administered immediately before and after ET.

Group 1: Acupuncture treatment based on the traditional Chinese medicine (TCM) style of acupuncture. For women randomized to receive acupuncture the initial treatment includes core points Guilai ST-29, Guanyuan Ren-4, Qihai Ren-6, Sanyinjiao SP-6, Xuehai SP-10, plus up to five additional points based on a TCM pattern differentiation. Two subsequent treatments will be administered on the day of ET pre and post transfer. Points administered on the day of ET include Diji SP-8, Xuehai SP-10, Taichong LR-3, Guanyuan Ren-4, one point from Shenmen HT-7, Neiguan PC-6, or YinTang, Baihui DU-20, Taixi KD-3, Zusanli ST-36, Sanyinjiao SP-6, and auricular points Shenmen and Zhigong. Manual acupuncture will be performed with needles inserted using the Park device [18], a supporting tube that facilitates maintenance of blinding for the participant. Needles will be inserted to a depth of not greater than 2 cm and retained for 25 min. The insertion of the acupuncture needle into an acupuncture point typically generates a range of sensations called ‘de qi’, this sensation will be maintained during the initial treatment on days 6 to 8, and during the pre-embryo treatment only. Points will be inserted bilaterally except for acupuncture points located on the Ren and Du points and YinTang point.

Group 2: Placebo control. This group will receive placement of non-invasive Park sham needles [18]. The Park needle has been shown to be an effective device for blinding in RCT [18]. These needles have a retractable needle shaft, a blunt tip, and skin penetration does not occur, and the needles have a supporting device. The acupuncturist will hold the ‘needle’ in place with one hand, while moving the handle of the needle with the other hand, so the shaft disappears into the handle. The needle is inserted through Park supporting device. The location of sham non-acupuncture points are away from real points and are described in relation to anatomical landmarks and relationship to acupuncture channels. Thirteen sham points are described: three on the abdomen, four on the arm, two on the leg, one on the back, one on the forehead, one on the foot, and one on the ear. The duration of needling and treatment session is the same as for the acupuncture group.

Study group 3: Usual care only. For women who decline to be randomized and were not planning to have acupuncture, they will be invited to participate in a non-randomized group receiving standard care only group, and provide consent to participate in all data collection.

### **Outcome measures**

Our primary study endpoint will be the proportion of women reporting a live birth defined as the delivery of one or more living infants, >20 weeks gestation or 400 g or more birth weight. Our secondary endpoints will be the proportion of women reporting a clinical pregnancy defined as demonstration of fetal heart activity on ultrasound scan, measured at 7 to 8 weeks, miscarriage defined as a non-viable pregnancy prior to 12 weeks, quality of life using the MOS Short Form 36 (SF36) [19], anxiety using the Stait Trait Anxiety Inventory [20] and infertility self-efficacy measured by the Infertility Self-Efficacy Scale [21] at trial entry, 2 and 14 weeks from trial entry. We will also collect data on expectations, and the therapeutic alliance. Clinical data will be collected from the IVF center database. Other outcomes will be collected by postal questionnaires. Data on the safety of acupuncture and any adverse events will be collected from practitioner treatment notes (Figure 1**)**

**Figure 1 F1:**
[figure not shown]
Study design.

### **Sample size**

Our pilot data [17] were suggestive of a larger treatment difference; however we have chosen a more conservative 7% estimate of the clinical effect from acupuncture compared with the placebo control group. The proportion of women with a live birth for women with multiple cycle failures in the placebo control group in our previous study was 12.1% [17]. To detect a 7% increase in the proportion of women that report a live birth between the treatment and placebo control, with 80% power at the 5% significance level will require 449 women per group. We have allowed for a loss of 30% due to cancelled cycles, or no ET. A total sample size of 1,168 women is required.

We expect a larger treatment effect (10%) when comparing acupuncture and standard care. To detect a 10% increase in the proportion of women that report a live birth between the treatment and standard care, with 80% power at the 5% significance level will require 193 women in the non-randomized group. Allowing for a 30% loss, due to cancelled cycles, or no ET, 251 women in the non-randomized group are required.

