****Methods**:**

We will conduct a randomized controlled trial of acupuncture compared to placebo acupuncture.

Inclusion criteria include: women aged less than 43 years; undergoing a fresh IVF or ICSI cycle; and restricted to women with the potential for a lower live birth rate defined as two or more previous unsuccessful ETs; and unsuccessful clinical pregnancies of quality embryos deemed by the embryologist to have been suitable for freezing by standard criteria. Women will be randomized to acupuncture or placebo acupuncture. Treatment is administered on days 6 to 8 of the stimulated cycle and two treatments on the day of ET. A non-randomized cohort of women not using acupuncture will be recruited to the study. The primary study outcome is the proportion of women reporting a live birth. Secondary outcomes include the proportion of women reporting a clinical pregnancy miscarriage prior to 12 weeks, quality of life, and self-efficacy. The sample size of the study is 1,168 women, with the aim of detecting a 7% difference in live births between groups (*P* = 0.05, 80% power).

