### **Randomization and blinding**

Women will be allocated to a study group by a research nurse phoning the randomization service, prepared and based at the National Health and Medical Research Council Clinical Trials Centre, Sydney, Australia. The randomization sequence is computer generated and concealed via central allocation. There will be stratification by the number of ET cycles (2 to 6 and 6+), woman’s age (<38 years, and 38 to 42 years), and collaborating center. Randomization will be into two study groups, acupuncture and a placebo control using the non-invasive Park needle [18]. Study participants, care providers, the outcome assessors, and the analyst will be blind to study group allocation.

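### The 30% loss allowance was added as a 1.3 multiplier, so 1,168 women leave about 409 per arm, not 449, and the stated 80% power is not reached

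*Protocol article*

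**What the plan says.** The Sample size section takes the control rate from the pilot, where the live birth proportion among women with multiple failed cycles "in the placebo control group in our previous study was 12.1"%. The target is a gain of 7 percentage points over placebo, which "with 80% power at the 5% significance level will require 449 women per group". The loss allowance comes next: "We have allowed for a loss of 30% due to cancelled cycles, or no ET. A total sample size of 1,168 women is required".

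The following paragraph treats the usual-care cohort in the same way. It starts from 193 women and concludes: "Allowing for a 30% loss, due to cancelled cycles, or no ET, 251 women in the non-randomized group are required".

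The Methods part of the abstract repeats the headline: "The sample size of the study is 1,168 women, with the aim of detecting a 7% difference in live births between groups", at 80% power. The Randomization and blinding section confirms that the 1,168 are divided between two arms: "Randomization will be into two study groups, acupuncture and a placebo control using the non-invasive Park needle". With equal groups, that is 584 per arm.

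**The concern.** A loss of 30% is a fraction of the women recruited. To finish with a required number n, recruitment must be n/(1 − 0.30). Adding 30% to n gives less than that, because 1.3 × 0.7 = 0.91: after the loss, 9% of the required number is missing. The stated total looks like the second calculation.

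If so, three printed statements (449 per group for 80% power, a 30% loss allowed for, 1,168 in total) cannot all be true. They describe the design of the primary endpoint. A reader facing a null result would use them to judge how large an effect the trial could have missed, and would credit it with more power than it has under its own loss assumption.

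**Working it through.** **Inputs.** All are from the Sample size section: control rate 12.1%; difference 7 points, so 19.1% with acupuncture; 5% significance; 80% power; 449 per group; loss 30%; total 1,168; non-randomized group 193, raised to 251. The section states neither whether the test is two-sided nor whether a continuity correction was used. Both are inferred in step 1.

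**1. Reproduce 449.** With p₁ = 0.121, p₂ = 0.191, p̄ = 0.156, d = 0.07, z = 1.960 (two-sided 5%) and 0.842 (80% power):

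n = [1.960·√(2p̄(1−p̄)) + 0.842·√(p₁(1−p₁) + p₂(1−p₂))]² / d² = (1.0058 + 0.4299)² / 0.0049 = 420.6

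With the continuity correction:

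n_c = (n/4)·[1 + √(1 + 4/(n·d))]² = 448.7, so **449**, an exact match.

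The alternatives do not match: 421 uncorrected, 418 with unpooled variance, 417 by arcsine, 332 one-sided (360 with correction).

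**2. Reproduce 1,168.**

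| Step | Per arm | Total |
|---|---|---|
| Multiply by 1.3 | 583.7 → 584 | **1,168** (898 × 1.3 = 1,167.4) |
| Divide by 0.7 | 641.4 → 642 | 1,284 (1,283 if 898/0.7 = 1,282.9 is rounded once) |

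Only the multiplication gives the stated total. It is 115 or 116 women below the figure that a 30% loss requires.

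**3. Check the second calculation.** 193 × 1.3 = 250.9 → **251**, as stated. 193/0.7 = 275.7 → 276. Two separate matches to the factor 1.3 rule out rounding or coincidence.

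**4. What remains after a 30% loss.** 1,168 × 0.7 = 817.6, about 818, or 409 per arm. That is 449 − 409 = 40 short in each arm. The loss that 1,168 does absorb is 1 − 898/1,168 = 23.1%. For the cohort, 251 × 0.7 = 175.7, about 176, which is 17 short of 193.

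**5. Power for 12.1% versus 19.1%, two-sided 5%.**

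Power = Φ{[d − c − 1.960·√(2p̄(1−p̄)/n)] / √((p₁(1−p₁) + p₂(1−p₂))/n)}, with c = 1/n for the continuity correction and c = 0 without it.

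At n = 409, corrected: (0.0700 − 0.0024 − 0.0497)/0.02526 = 0.706, and Φ(0.706) = 0.760.

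| Women per arm | Corrected (the basis that gives 449) | Uncorrected |
|---|---|---|
| 449 | 80.0% | 82.5% |
| 409 | **76.0%** | 78.9% |

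Solving for the difference detectable with 80% power at 409 per arm from 12.1% gives 7.4 points (corrected) or 7.1 points (uncorrected).

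**6. The non-randomized comparison.** The article gives no standard-care rate. The expected advantage of 10 points over standard care, set against 19.1% with acupuncture, implies 9.1%. With 176 versus 409 women, unadjusted power for 9.1% versus 19.1% is 86% corrected and 89% uncorrected. It stays above 80% because the acupuncture arm is larger than 193.

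**The case against.** The strongest objection is intention to treat. The Data analysis section commits to it, and the Outcome measures section takes clinical data from the IVF center database. A woman with a cancelled cycle or no transfer is therefore not missing for live birth; she counts as having none. All 584 per arm would be analysed, and power depends on whom the 12.1% and 19.1% describe, which the article does not say. There are two readings:

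- *The rates apply to women who reach transfer.* Counting the other 30% as no live birth gives 0.7 × 12.1% = 8.5% and 0.7 × 19.1% = 13.4%. Power at 584 per arm is 73.7% corrected and 76.6% uncorrected. The shortfall remains.
- *The rates already apply to every woman randomized.* Power at 584 per arm is about 90% corrected and 91% uncorrected. But then cancelled cycles need no allowance, and the 30% in the Sample size section has no purpose.

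So the only reading that rescues the power claim contradicts the plan's own loss allowance.

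It can also be said that the effect is small, and that is fair. Power drops by 4 points on the plan's apparent method and ends about 1 point below target if no correction is used. The 12.1% is a pilot estimate, and the 7 points were chosen as conservative against the pilot. These facts limit the consequence; they do not make the printed figures agree.

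The reassurance about the non-randomized group does depend on the assumed standard-care rate. At 12.1% versus 22.1%, power is 79.6% corrected and 83% uncorrected. That comparison is observational and adjusted for confounders, so its nominal power carries little weight either way.

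**Conclusion.** The point holds: the sample-size statement is wrong as written. The 30% allowance was applied as an uplift of 30%, once for the randomized arms and once for the cohort. The trial as sized covers a 23% loss. If the loss is 30%, the primary comparison has about 76% power for 7 points, or 79% without the continuity correction.

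The counts (409 per arm, 23.1%, 176) follow from the printed figures alone. The 76% rests on a two-sided, continuity-corrected calculation, inferred because it reproduces 449 exactly, and on the section's own treatment of women without transfer as lost. The error is certain and its effect on power is modest. It does not invalidate the trial.

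**What to change.** Leave recruitment at 1,168 and correct the Sample size section in one of two ways:

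1. State that 1,168 women allow for a loss of 23%. This is the simpler choice. The abstract can then stand, since it does not mention the 30%.
2. Keep the 30% and state that about 409 women per group would remain, giving 76% power for a 7-point difference, or 80% power for 7.4 points. The 80% power in the abstract must then change to match. The text should also say how this count of women with a transfer relates to the intention-to-treat analysis.

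Correct the cohort figure likewise: 251 women allow for a 23% loss, or leave 176 after a 30% loss.

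The cost is wording only. The stated power or loss allowance becomes slightly less favourable, and no additional women, procedures or changes to the analysis are needed. The article reports that recruitment is in progress, so the correction can still be made before results are known.

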### **Data analysis**

Data will be analyzed by a statistician based at UWS blind to study group. Analyses of the endpoints will undertake an ‘intention to treat’ approach and compare differences in the primary and secondary endpoints between groups. The primary analysis will compare the proportions of patients with live births. Logistic regression will be used to identify baseline variables which are associated with outcomes. Linear models will be used to test for between group differences in the continuous outcome measures (for example, health status).

Subgroup analyses will be stated *a priori*, for example influence of stimulation doses, long- or short-acting stimulation cycle. Levels of significance will be reported at *P* < 0.05.

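### The 80% power is calculated for women who reach embryo transfer, but the stated intention-to-treat analysis keeps all randomized women

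*Protocol article*

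**What the plan says.** The Sample size section of the protocol article takes the placebo live birth rate from the investigators' earlier study: among women with "multiple cycle failures in the placebo control group in our previous study was 12.1" per cent. It seeks an increase of 7 percentage points and concludes that this "will require 449 women per group" at 80% power and the 5% level. It then adds an allowance with one stated cause: "We have allowed for a loss of 30% due to cancelled cycles, or no ET". The result is "A total sample size of 1,168 women is required", or 584 per group. The same 30% allowance, for the same reason, takes the non-randomized group from 193 to 251.

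The Data analysis section states: "Analyses of the endpoints will undertake an ‘intention to treat’ approach and compare differences in the primary and secondary endpoints between groups". Under Outcome measures, the primary endpoint is a proportion of women, with no restriction to women who had a transfer. Under Interventions, women see the study acupuncturist after randomization, and "The initial diagnosis and treatment will take 60 to 90 minutes undertaken on days 6 to 8 of the stimulated IVF cycle". Cancellation after that session, or failure to reach ET, therefore happens after randomization and after treatment has begun.

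**The concern.** The two sections treat the same women differently. In the sample size they are subtracted as loss, so the 449 per group are those left after cancelled cycles and absent transfers. In an intention-to-treat analysis they are not lost. They were randomized, the IVF center database records what happened, and a woman with no transfer is counted as having no live birth from that treatment.

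Two things are at stake. First, the stated power does not describe the stated primary analysis. Keeping these women enlarges the denominator. If the planning rates were per woman with ET, it also shrinks both rates and the difference between them. Second, the 7-point target may not be the difference that the primary analysis estimates. A reader of the final report needs to know whether 7 points is per woman randomized or per woman transferred.

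**Working it through.** **Inputs (protocol article, Sample size).** p1 = 0.121; p2 = 0.121 + 0.07 = 0.191; power 80%; level 5%; equal groups; allowance 30%; total 1,168. Sidedness is not stated; two-sided is assumed because it reproduces the plan's figure.

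**1. Reproduce the plan.** With p̄ = (p1 + p2)/2 and d = p2 − p1:

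n0 = [1.960 √(2p̄(1−p̄)) + 0.842 √(p1(1−p1) + p2(1−p2))]² / d² = 420.6

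Continuity-corrected: n = (n0/4) [1 + √(1 + 4/(n0 d))]² = 448.7, rounded up to **449**, as stated.

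Inflation: 449 × 1.3 = 583.7, rounded up to 584; 2 × 584 = **1,168**, as stated. Dividing by 0.7 would give 642 per group (1,284), so the plan multiplied.

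**2. Power formula for the checks.**

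Power = Φ{ [d − c − 1.960 √(2p̄(1−p̄)/n)] / √[(p1(1−p1) + p2(1−p2))/n] }

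where c = 1/n with the continuity correction and c = 0 without it. At n = 449 and 12.1% v 19.1% this gives 80.0% corrected (82.5% uncorrected). That is the plan's own statement, and it holds for 449 analysed women per group.

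**3. Reading A: 12.1% and 7 points are per woman with ET; 30% have no ET and no live birth.**

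- Placebo: 0.7 × 0.121 = 0.0847
- Acupuncture: 0.7 × 0.191 = 0.1337
- Difference: 0.0490, or 4.9 points
- At n = 584, corrected: (0.0490 − 0.0017 − 1.960 × 0.01825)/0.01820 = 0.633, so power = **73.7%**
- Uncorrected: **76.6%**
- For 80% power: 676 per group corrected (1,352 in total), 635 uncorrected (1,270)

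**4. Where the shortfall in reading A comes from.**

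| Step | Per group | Rates | Power, corrected (uncorrected) |
|---|---|---|---|
| Plan's calculation, ET only | 449 | 12.1% v 19.1% | 80.0% (82.5%) |
| ITT, 30% without ET, inflated by 1/0.7 | 642 | 8.5% v 13.4% | 77.9% (80.4%) |
| ITT, 30% without ET, inflated by 1.3 | 584 | 8.5% v 13.4% | 73.7% (76.6%) |

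Dilution costs about 2 points (80.0 to 77.9). The inflation step costs about 4 (77.9 to 73.7).

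Multiplying by 1.3 covers a loss of 1 − 449/584 = 23%. If only 23% have no ET, power at 584 per group under intention to treat is 78% (corrected) to 81% (uncorrected).

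With 30% lost from 584, about 0.7 × 584 = 409 per group reach ET. Even an ET-only comparison then has 76.0% (78.9%).

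**5. Reading B: 12.1% and 7 points are already per woman randomized.** Nobody is removed and no inflation was needed: 2 × 449 = 898 women would do. At 584 per group and 12.1% v 19.1%, power is **89.6%** (91.0% uncorrected).

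**The case against.** The strongest reply is that a sample size allowance is a planning margin, not an analysis rule. The Data analysis section already fixes intention to treat, nothing in the article excludes women without ET, and exact analysis sets are commonly left to the full protocol or the analysis plan. This stands. A reader might infer that the plan permits two primary analyses, one of them open to selection after treatment has begun. The article does not support that: it names one approach, and the selection problem would arise only through an exclusion that it nowhere states.

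A reader might also infer that 80% for 7 points describes no analysis at all. That goes too far, since it is correct for an ET-only comparison with 449 women per group.

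It is fair, too, that most of the drop to 74% is due to the inflation arithmetic, that at 23% without ET the power is close to the stated 80%, and that the denominator of 12.1% lies in a study not shown here. Nor does the endpoint definition tie live birth to a cycle or a time limit, so counting every woman without ET as having no live birth is a reasonable assumption rather than a written rule.

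What the objection does not remove is that the only stated reason for the 30% is an event that does not take a woman out of an intention-to-treat analysis.

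**Conclusion.** The concern holds as a mismatch between the population used for power and the population to be analysed. At the stated 30%, the 80% is not the power of the intention-to-treat comparison of 584 per group on either reading of 12.1%: it is 74% to 77% on reading A and about 90% on reading B. The direction cannot be settled from the article, so it would be wrong to call the trial simply underpowered.

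These figures assume a two-sided 5% test, equal groups, no live birth among women without ET and, on reading A, the same share without ET in both groups.

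This should be fixed, but it does not threaten validity: if the stated analysis is followed, the effect estimate is not biased by this point.

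**What to change.** - State the denominator of the 12.1%: per woman randomized or per woman with ET.
- Give the expected share of women not reaching ET in place of the loss allowance. Express the expected rates and difference per woman randomized, and restate the power for 584 per group on that scale: 74% to 77% (8.5% v 13.4%) if the 12.1% is per woman with ET and 30% have none, or about 90% (12.1% v 19.1%) if it is per woman randomized. Only the figures that match the true denominator should go in.
- Confirm that the primary analysis keeps all randomized women in their allocated group, with a cancelled cycle or no ET counted as no live birth.
- Label any ET-only comparison as supportive and conditional on a post-randomization event.
- Clarify the same 30% allowance for the non-randomized group.

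The cost is wording in the protocol and analysis plan, with no added patients or data. The downside is that the stated power may become slightly less favourable. Holding 80% on reading A would take 1,270 to 1,352 women, which is not asked for here. As recruitment is under way, the text should be settled before outcomes are seen by group.
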